## Abstract

**Background:**

Highly active antiretroviral therapy produces a significant decrease in HIV-1 replication and allows an increase in the CD4 T-cell count, leading to a decrease in the incidence of opportunistic infections and mortality. However, the cost, side effects and complexity of antiretroviral regimens have underscored the immediate need for additional therapeutic approaches. Statins exert pleiotropic effects through a variety of mechanisms, among which there are several immunoregulatory effects, related and unrelated to their cholesterol-lowering activity that can be useful to control HIV-1 infection.

**Methods/design:**

Randomized, double-blinded, placebo controlled, single-center, phase-II clinical trial. One hundred and ten chronically HIV-1-infected patients, older than 18 years and naïve for antirretroviral therapy (i.e., without prior or current management with antiretroviral drugs) will be enrolled at the outpatient services from the most important centres for health insurance care in Medellin-Colombia. The interventions will be lovastatin (40 mg/day, orally, for 12 months; 55 patients) or placebo (55 patients). Our primary aim will be to determine the effect of lovastatin on viral replication. The secondary aim will be to determine the effect of lovastatin on CD4+ T-cell count in peripheral blood. As tertiary aims we will explore differences in CD8+ T-cell count, expression of activation markers (CD38 and HLA-DR) on CD4 and CD8 T cells, cholesterol metabolism, LFA-1/ICAM-1 function, Rho GTPases function and clinical evolution between treated and not treated HIV-1-infected individuals.

**Discussion:**

Preliminary descriptive studies have suggested that statins (lovastatin) may have anti HIV-1 activity and that their administration is safe, with the potential effect of controlling HIV-1 replication in chronically infected individuals who had not received antiretroviral medications. Considering that there is limited clinical data available on this topic, all these findings warrant further evaluation to determine if long-term administration of statins may benefit the virological and immunological evolution in HIV-1-infected individuals before the use of antiretroviral therapy is required.

**Trial registration:**

Registration number NCT00721305.

## Background

Type-1 human immunodeficiency virus (HIV-1), the etiologic agent of the acquired immunodeficiency syndrome (AIDS), causes a chronic disease characterized by a progressive loss of CD4+ T cells associated with other quantitative and qualitative alterations of the immune response. Currently, HIV-1 infection is among the most important public health problems around the world: at the end of 2007, there were around 33 million people infected, 2,5 million new cases were diagnosed and 2,1 million HIV-1-infected individuals died as a consequence of HIV-1-derived clinical complications [1]. In Colombia, is has been estimated that more than 190.000 persons are infected with HIV-1 (calculated prevalence: around 0.7%), and 24.000 deaths due to HIV-1 infection were reported between 1987 and 2007 [1,2].

The dysregulation of the immune response appears early during HIV-1 infection when individuals gradually lose their T lymphocyte proliferative responses to recall antigens, alloantigens and mitogens, before the severe reduction in CD4 T-cell count appears. In addition to the direct elimination of CD4 T cells, HIV-1 impair immune function directly through the immunosuppressive effect of viral proteins and by a state of uncontrolled immune activation that leads to immunosuppression and accelerated CD4 T-cell death [3-5].

The current treatment for HIV-1 infection is highly active antiretroviral therapy (HAART), which decreases viral replication and plasma HIV-1 RNA levels, allowing partial immune restoration that associates with a decrease in the incidence of opportunistic infections and mortality [6]. However, after HAART is discontinued there is a rebound in viral load and a decrease in CD4+ counts to similar levels than before HAART administration. In addition, potent antiretroviral therapy administered for several months is unable to eliminate HIV-1 tissue reservoirs effectively and do not lead to a full recovery of the immune response [7].

On the other hand, international guidelines for HAART therapy in chronically HIV-1-infected adults recommend beginning these regimens in those individuals with an AIDS-defining illness, in HIV-1 positive pregnant women, and in patients with a CD4+ T-cell count lower than 350 cells/μL [8]. In this sense, too many patients with an early diagnosis of HIV-1 infection would be without antiretroviral therapy during several years, with a persistent viral replication and a progressive lymphoid tissue damage, which may affect the level of immune restoration achieved after the late onset of HAART. Furthermore, the cost and complexity of HAART regimens, the recommended delayed beginning of HAART in adults chronically infected with HIV-1, the growing list of long-term side effects, and the eventual development of resistance have underscored the immediate need for additional therapeutic approaches.

Statins are mainly known for their plasma cholesterol-lowering properties and are widely used for the prevention of cardiovascular diseases [9,10]. They, however, also have pleiotropic actions through a variety of mechanisms, among which there are several virological and immunoregulatory effects that are unrelated to their cholesterol-lowering activity [11-13]. Depletion of cholesterol alters the capacity of a cell to form lipid rafts, and numerous studies have shown that HIV-1 requires lipid rafts for several key stages of its replication cycle [14,15]. Moreover, some evidence suggests that statins alter the intracellular signals dependent on Rho GTPases [16], the functional activity of LFA-1/ICAM-1 adhesion molecules [17], the expression of the CCR5 coreceptor and the secretion of RANTES [18], and may exert significant modulatory effects on the balance of the cytokine network in human beings [19,20]. Based on these immunomodulatory properties, statins are being evaluated in the treatment of diseases beyond classic cardiovascular conditions [21]. Therefore, statins therapy might modulate the immune system function in HIV-1-infected individuals, affecting the clinical course of this infection. Whether these observations translate into significant clinical interactions is uncertain, and very limited clinical data are available on this topic.

We hypothesize that the long-term use of statins will benefit the overall evolution of HAART naïve HIV-1-infected individuals, having the following effects: i) decreasing plasma viral load; ii) increasing blood CD4 T-cell count; iii) restoring the immune system function; and iv) decreasing the frequency of morbidity and mortality. To evaluate this hypothesis, this investigation is aimed to explore the effect of lovastatin (oral intake, 40 mg/day during one year) on viral load and CD4 T-cell count, adaptive immune parameters, cholesterol metabolism and Rho GTPases function, and clinical evolution of chronically HIV-1-infected individuals who are HAART naïve.

## Methods/design

### Study Design

Randomized, double-blinded, placebo-controlled, phase II clinical trial.

### Study Population

One hundred and ten (110) chronically HIV-1 infected patients without antiretroviral treatment.

The inclusion criteria will be the following:

- Asymptomatic HIV-1 positive individuals, with age ≥ 18 years, who are HAART naive

- HIV-1 infection confirmed by: a) any positive western blot at least six months before admission to the study; or b) within the last six months by a western blot that includes the p31 and p66 bands

- Detectable viral load but less than 100,000 copies/mL

- CD4+ T cell count ≥ 350 cells/μL

The exclusion criteria will be the following:

- Inability or unwillingness of patients to give written informed consent

- Main residence outside Medellin and its metropolitan area, or any indication of difficulties in the follow-up period

- Participation in other clinical trials

- Evidence that the patient will exhibit low adherence to intervention and follow-up (Morisky-Green test)

- Pregnancy or breastfeeding

- Any type of antiretroviral treatment before admission to the study, and therapy with lipid-lowering drugs during the last six months

- Antecedents of allergy, contraindications or intolerance to statins

- Patients receiving medications which can generate relevant interactions with lovastatin: clarithromycin, erythromycin, azithromycin, itraconazole, ketoconazole, nefadozone, cimetidine, rifampin, phenobarbital, carbamacepin, phenitoin, gemfibrozil.

- Unwillingness to avoid the consumption of Citrus paradise (grapefruit juice) or Saint John's Wort (Hypericum)

- Chronic active hepatitis (B or C)

- Any hepatocellular disease, indicated by elevation of liver enzymes (AST or ALT) more than twice the upper limit of reference values

- Renal failure, indicated by serum creatinine ≥ 2 mg/dL

- Myopathy, indicated by an elevation of creatine phosphokinase (CPK) more than five times the upper limit of reference values

- Infection or acute disease that requires inpatient treatment

- Active substance-related disorders.

- Medical indication for using lipid-lowering drugs

### Randomization

The treatment assignment ratio will be 1:1, fixed throughout the study. The allocation sequence will be developed by a statistician in the Data Coordinating Center (DCC) using randomly permuted blocks of size 2, 4 and 6 generated by a random number generator (*ralloc *program, Stata co. 8.2, College Station, TX, USA). Once the sequence is generated, it will be matched with sequential numbers between 001 and 110 and given to the manufacturer for labelling the blisters containing the pills with lovastatin or placebo. The allocation sequence will remain in a confidential file in the DCC unknown for the clinician investigators, the patients, and the pharmacists who dispensed the interventions. This sequence will be disclosed only after study termination for data analysis, or at request by the Data Safety Monitoring Board (DSMB).

### Allocation concealment mechanism

The manufacturer will deliver both interventions (lovastatin and placebo) to the clinical investigators labelled only with the number code assigned from the list given by the DCC. Neither the investigators nor the pharmacists will know the actual content of the pills, as they will be contained in identical blisters and their physical characteristics will be the same (size, shape, colour and smell). The complete treatment course for one year, dispensed monthly, will be packed in sealed boxes equally labelled with the corresponding number, unique for each participant. Each treatment will be allocated and opened only for the sequential participant intended to enrol after the verification of eligibility criteria. The pharmacists will handle the interventions and will be responsible for their maintenance under lock and key. The dosage for lovastatin is 40 mg per day, represented by two pills to take each night; for this reason both interventions will be dispensed to fulfil two pills per night.

### Clinical follow-up

Before the enrolment and monthly during the study, all the patients will have a complete clinical evaluation performed by a physician who is blinded for the intervention assigned to each patient. Before the intervention (day 0) and 30, 180 and 360 days of study, blood samples will be collected to perform laboratory analysis (transaminases, CPK, serum lipid profile). The intervention will be stopped in presence of serious adverse events, a three-fold increase in serum transaminases or a five-fold increase in CPK. In order to preserve the blinding process, only the first value of serum lipid profile (day 0) will be known by the clinical investigators (eligibility criteria). Afterwards, for the samples at 180 and 360 days of following, a medical safety monitor in the DCC will receive the report directly from the laboratory.

The following clinical and pharmacotherapy parameters will be evaluated monthly for one year, during the medical control visits:

- Tolerance to medications and adverse events

- Adherence to therapy (lovastatin or placebo) and prevention of withdrawals

- Incidence of infections (opportunistic and non-opportunistic)

- Incidence of non-infectious diseases defining AIDS

- Hospitalizations due to diseases related to progressive HIV-1-infection

- Death due to diseases related to progressive HIV-1-infection

### Interventions and safety of statins

After the first medical appointment and then monthly, each participant will receive the whole therapy for 1 month (60 tablets of lovastatin or placebo) from the pharmacist who also evaluates adherence to the intervention and gives usage recommendations. The statins are well tolerated by most persons; they have proven to be extremely safe in the vast majority of patients. Few significant side effects have been observed in clinical trials, and post-marketing reports of adverse events have been very limited when considered in comparison to a very large number of persons safely using them. The main risks of statins are elevation of hepatic enzymes, and myopathy. Elevated hepatic transaminases generally occur in 0.5% to 2.0% of patients and are a dose-dependent effect; progression to liver failure specifically due to statins is exceedingly rare. Myopathy induced by stain is also rare. Mild gastrointestinal symptoms (e.g., constipation, flatulence, dispepsia, and abdominal pain), are the most common adverse effects of lovastain. Thus, a lovastatin dose of 40 mg/day is well tolerated with low discontinuance rates (lower than 2%). [22]

### Retention and adherence to the trial

The study is conducted in the outpatient services from the most important centres for health insurance care in the city of Medellín (northwest region of Colombia). The staff physicians are informed of the study protocol and they are attentive to eligibility criteria in their daily consultation. Once a potential participant is detected, her/his attending physician will give her/him information regarding the clinical trial and ask for permission to give both complete identification (full name, identity number) and contact phones (main and alternative) to the trial coordinators. They will call those potential participants and invite them to an informative meeting with the clinical investigators. In this interview, eligibility criteria should be applied including laboratory screening. When the results come out, they are sent to the trial coordinator who should again contact the potential participant for a recruiting visit, in which informed consent will be signed.

To keep permanent contact with potential and recruited participants, the trial coordinator will be available through a 24-hour mobile phone and e-mail messaging. Also, she should maintain a constant two-way communication with the HIV-attention program to constantly detect new potential candidates. At the end of each consultation, the next appointment will be scheduled in advance, giving a card with emergency phones and information. All participants will be contacted by the trial coordinator at least two days before the scheduled visit to confirm it and to re-schedule, if necessary. If any of the potential or recruited participants are not available, an active search for updated contact information should be performed beginning by reviewing the health insurance database and also calling the alternative phone numbers provided. Special attention should be given to the basal condition of individuals at the time of the programmed laboratory tests. Recommendations are given in each consultation, and the participants will be encouraged to call the trial coordinator to solve doubts or questions any time.

### Study outcomes

The efficacy of lovastatin to control HIV-1 replication allowing an improved immune reconstitution will be determined by primary and secondary outcomes. The primary outcome will be the viral load measured as RNA copies per mL of peripheral blood, and the secondary outcome will be the CD4 T-cell count measured as cells per μL of peripheral blood; both determined at enrolment, and 6 and 12 months after the intervention.

The tertiary or exploratory outcomes will be the following (determined at enrolment, and 6 and 12 months of interventions, unless indicated otherwise):

- Absolute number per μL of peripheral blood of CD8+ T lymphocytes and the CD4/CD8 ratio

- Basal expression of immunological activation markers (CD38 and HLA-DR) on CD4+ and CD8+ T lymphocytes

- Concentration of total serum cholesterol

- Concentration of cellular cholesterol

- Functional activity of LFA-1 and ICAM-1

- Activity of Rho GTPases

- Monthly frequency and type of: infections, non-infectious AIDS defining diseases, hospitalizations

- Mortality due to an HIV-1/AIDS related cause

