### Biostatistical considerations

Primary hypothesis: The use of lovastatin (40 mg/day during one year) compared with placebo in HIV-1-infected individuals who are naïve for HAART, should result in a reduction of 50% or higher in viral load and an increase of 20% or higher in CD4 T cell count.

Documentation of outcome and follow-up: Primary and secondary outcome measures will be documented by investigators and research assistants masked to the subject's intervention group assignment.

Sample size and power: Based on a pilot test performed on 40 patients treated at the infectious diseases service, Hospital Universitario San Vicente de Paul (Medellin, Colombia), the baseline values for the primary and secondary outcome measures are as follows:

Mean viral load = 55,000 copies/mL; SD = 80,000 copies/mL

Mean CD4+ T cell count = 500 cells/mL; SD = 180 cells/mL

These outcomes, determined 6 and 12 months after the intervention, are longitudinal data with correlated measurements, and they need special considerations for calculation of power and sample size. In addition to the usual requirements of type I error, type II error, variation measurement and meaningful difference to be detected in longitudinal studies, it is necessary to know the number of repeated observations and an estimate of the correlation among them. The meaningful difference may be expressed as a time-averaged difference in response between groups. Assuming a fixed correlation of 0.8 among the three different measures of viral load, and a time-average difference of 50% between groups (i.e., a decrease of 22,500 copies/mL from the baseline value), with an alpha error of 0.05 and a beta error of 0.2, the sample size required is 55 patients per group. This sample size has more than 90% power to detect an increase of at least 20% in the baseline CD4+ T cell count. There will be not corrections for losses to follow-up or non-adherence, as the study is intended as a pilot phase II trial.

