### Interim monitoring

An independent DSMB comprising three members with expertise in statistics, epidemiology and infectious diseases will be responsible for the interim monitoring process. The statistician at the Data-Coordinating Center will be the only person with access to the full database and he will provide the required information, both overall for the interim quality assurance and specific by treatment group (efficacy and safety) exclusively for the DSMB. The first interim monitoring will be conducted when the study participants complete six months of evaluation. The second interim analysis will be conducted when all the patients complete nine months of evaluation. Stopping guidelines for efficacy monitoring will be determined for the primary and secondary outcomes according to the modified O'Brien-Fleming procedure. With this procedure, the values for statistical significance are 0.0006 and 0.0151 in the first (α_1_) and second (α_2_) interim analyses, respectively, for a final significance (α) of 0.0471. Stopping guidelines for safety are left at discretion of the DSMB, with an expected rate of adverse events (hepatic or muscle enzymes elevations) less than 1%. Stopping guidelines regarding futility are not considered and this was agreed in a meeting with the DSMB.

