The β coefficient obtained with this procedure for the X variable is the estimated time-averaged change in the outcome measure in the lovastatin group compared with placebo, and its p-value is given by the Wald statistic . We will use the *xt *of commands from the statistical package Stata (StataCorp, 2007: Release 10, College Station, Texas, USA) for the proposed analysis of cross-sectional time-series datasets. Specifically, the command *xtgee *will evaluate population-averaged panel-data models using GEE. Although the expectation is that randomization assists in balancing known and unknown prognostic factors in a randomized clinical trial, this assignment process is not a guarantee against the possibility that estimates of treatment effect be modified by covariate imbalance. Accordingly, the estimated time-averaged change in the outcome measure for lovastatin vs. placebo will be adjusted by the most important prognostic factors (baseline CD4+ T cell count, baseline viral load, and adherence to the treatment) considered as additional independent variables in the same GEE model.

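### The hypothesis is a percentage reduction in viral load, but outcome, sizing and coefficient are in raw copies/mL; log10 viral load in the same GEE would match it at no loss of power

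*Protocol article*

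**What the plan says.** Four places in the protocol article bear on the scale of the primary outcome.

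- **Study outcomes:** "The primary outcome will be the viral load measured as RNA copies per mL of peripheral blood", determined at enrolment and at 6 and 12 months.
- **Biostatistical considerations, hypothesis:** lovastatin "should result in a reduction of 50% or higher in viral load", which is a relative effect.
- **Biostatistical considerations, sample size:** the planning values are "Mean viral load = 55,000 copies/mL; SD = 80,000 copies/mL", and the 50% is turned into an absolute difference, "a decrease of 22,500 copies/mL from the baseline value".
- **Analysis plan:** a GEE with exchangeable correlation and Huber-White variance, whose coefficient is read as "the estimated time-averaged change in the outcome measure in the lovastatin group compared with placebo". Baseline viral load is one of the adjustment covariates.

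Neither a log transformation nor a log link is named. Study Population restricts entry to a detectable viral load below 100,000 copies/mL.

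**The concern.** The question is multiplicative and the planned quantity is additive. A difference in arithmetic means does not directly estimate a percentage reduction. Its size for a given percentage depends on the viral load of the patients who happen to enrol.

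The pilot SD is 80,000/55,000 = 1.45 times the mean of a variable that cannot be negative, so the pilot distribution must be strongly right-skewed. On such a scale the variance of the coefficient is driven by the highest values, and there are only 55 patients per arm. What is at stake is whether the primary estimate answers the stated hypothesis, and how precisely it does so.

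**Working it through.** **Inputs from the document.** Mean 55,000; SD 80,000; difference 22,500; correlation 0.8; three measures (baseline, months 6 and 12); alpha 0.05, taken as two-sided; 80% power; 55 per arm; entry below 100,000.

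**Inputs assumed.** Lognormal data, a constant multiplicative effect, and a correlation of 0.8 on the log scale. The document gives no log10 SD, so a range is shown.

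**1. The plan's own figure.** For a time-averaged difference, n = 2(1.96 + 0.842)² × SD² × f / difference², with f = (1 + 2 × 0.8)/3 = 0.867.
- Raw scale: 2 × 7.849 × (80,000/22,500)² × 0.867 = 172 per group, not 55.
- With one baseline as covariate and two follow-ups, f = 0.9 - 0.64 = 0.26, which gives 52. Change from baseline with three follow-ups (f = 0.267) gives 53.

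So 55 is approximately recoverable, but only with a baseline correction that the sample size paragraph does not state. That, and the fact that half of 55,000 is 27,500 and not 22,500, are separate points.

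**2. The same formula on log10.**
- A lognormal variable with the stated mean and SD has sigma = sqrt(ln(1 + (80/55)²)) = 1.066, or 1.066/2.303 = 0.463 on log10, with median about 31,200.
- A 50% reduction is log10(0.5) = -0.301.
- The standardised effect is 0.301/0.463 = 0.65, against 22,500/80,000 = 0.28 or 27,500/80,000 = 0.34 on raw copies.
- The time-averaged formula then needs 33 per group. With baseline adjustment it needs 10, against 52 on raw copies.
- For assumed log10 SDs of 0.4, 0.6, 0.7 and 0.9, the time-averaged n is 25, 55, 74 and 122; the baseline-adjusted n is 8, 17, 23 and 37.

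**3. What a 50% effect is on the raw scale.**
- Pilot-like population: 0.5 × 55,000 = 27,500 (about 27,000 in simulation).
- With the entry limit: a = (ln 100,000 - ln 31,159)/1.066 = 1.094. The placebo mean at follow-up is 55,000 × Φ(1.094 - 0.8 × 1.066)/Φ(1.094), about 37,900. Half of that is about 19,000 (18,800 in simulation).
- On log10 the effect is -0.30 in both populations.

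**4. Influence.** In simulated pilot-like control arms of 55, the six highest patients contribute about 40% of all copies. With the entry limit the share is about 32%.

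**5. Simulated power.** 55 per arm, average of months 6 and 12, robust Wald test, 2,000 to 3,000 trials per setting; figures differ slightly between repeat runs.

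| Setting | Raw | log10 |
|---|---|---|
| 50%, no entry limit, unadjusted, log10 SD 0.46 | 81% | 94-95% |
| 50%, entry limit, unadjusted, 0.46 | 97-98% | 98% |
| 50%, entry limit, baseline-adjusted, 0.46 | near 100% | near 100% |
| 30%, entry limit, baseline-adjusted, 0.46 | about 79% | 92-93% |
| 50%, entry limit, baseline-adjusted, 0.6 | 95% | 99.9% |
| 50%, entry limit, baseline-adjusted, 0.7 | 83-85% | 99% |

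Under no effect, rejection is close to 5% on both scales (unadjusted: 4.6% raw, 5.9% log10).

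**The case against.** **Is the scale really fixed?** Copies per mL could be only the unit of measurement, and the GEE is written for a generic outcome, so an unshown analysis plan might transform it. Part of this stands: the Analysis plan nowhere says that the response is untransformed. But the outcome definition, the planning difference and the reading of the coefficient all point to copies/mL. The mismatch with a percentage hypothesis is therefore in this text.

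**Stronger readings that a reader might infer, and that the document does not support:**
- *The raw analysis is invalid.* It is not. Huber-White standard errors are specified, and type I error is close to nominal.
- *Log10 would rescue power at the planned effect.* With the baseline adjustment that the plan names and the entry limit, both scales are near 100% for 50% at log10 SD 0.46. The 30% effect is not in the document, and SDs of 0.6 or more are assumptions.
- *Enrolled patients will have an SD above the mean.* Values between 0 and 100,000 with mean 55,000 cannot have a baseline SD above sqrt(55,000 × 45,000), about 49,750. The pilot values therefore cannot all be eligible, and skew at entry will be milder.
- *Patients with low viral load get almost no weight.* In an exchangeable GEE with complete data every patient has equal weight; high values dominate the variance.
- *The coefficient cannot be set against the 50%.* It can be compared with the planned copies/mL difference, or divided by the placebo mean to give a reduction in the mean. It is not itself the percentage.

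**Does log10 ask a different question?** Yes. A ratio of geometric means replaces a difference in arithmetic means, and the two agree as percentages only if the effect is constant and multiplicative.

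**Conclusion.** The point holds as a mismatch between hypothesis and estimand, with an efficiency cost of uncertain size. The mismatch does not depend on the power figures: one 50% effect corresponds to about 27,000 or about 18,800 copies/mL depending on enrolment, but to -0.30 log10 in either population.

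Under lognormal data and a multiplicative effect, log10 was at least as powerful in every setting examined. The gain ranges from nothing at the planned effect and log10 SD 0.46 to about 14 points for a 30% effect at that SD, or about 15 points for a 50% effect at SD 0.7. The change should be made, but leaving the raw scale would not invalidate the trial.

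**What to change.** - Define the primary response as log10 copies/mL. Keep the same GEE, exchangeable correlation and robust variance, with log10 baseline viral load as the covariate.
- Report 10^beta with its confidence interval as the ratio of geometric means; 1 - 10^beta is the proportional reduction.
- State the target as -0.30 log10, and redo the sizing with the log10 SD of those among the 40 pilot patients who meet the entry limit.
- Prespecify how follow-up values below the assay's detection limit are handled, since log10 needs a rule.
- Use the same scale for the efficacy looks under Interim monitoring.

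The cost is protocol and analysis plan wording and one recalculation from data already held. No visit, assay or patient burden changes. The price is that the primary estimate no longer describes arithmetic means; the raw-scale difference can be kept as a secondary summary.

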### Analysis plan

The overall efficacy will be established with an intention-to-treat principle, in which the patients will be analyzed in the treatment group to which they were assigned by randomization. The outcomes viral load and CD4 T cells count, as well as most of tertiary/exploratory outcomes, are longitudinal data with repeated measurements and they require special statistical methods to account for the correlation among observations. To analyze this kind of clustered data it is necessary to model both the regression of *Y *(the outcome measure) on *x *(the intervention) and the within-cluster dependence. In a marginal model, the regression of *Y *on *x *and the within-cluster dependence are modelled separately with the application of the statistical method called generalized estimating equations (GEE), which was designed to provide valid regression inferences with correlated data [24].

When the regression analysis for the time-averaged difference in response between groups is the primary interest, as for our research, the *β *coefficient can be estimated by solving the estimating equation

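### The mortality outcome counts only HIV-related deaths, the two descriptions of hospitalisation disagree, and the harms data being collected are in no listed outcome

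*Protocol article*

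**What the plan says.** **Hypothesis.** The last paragraph of the Background expects long-term statin use to reduce illness and death (item iv). It sets no limit on cause.

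**Outcomes.** Study outcomes names viral load as primary, CD4 count as secondary, and a tertiary list. The clinical items in that list are "Monthly frequency and type of: infections, non-infectious AIDS defining diseases, hospitalizations" and "Mortality due to an HIV-1/AIDS related cause". Total serum cholesterol is listed. Adverse events, transaminases and CPK are not.

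**Recording.** Clinical follow-up sets out what is assessed at the monthly visits. It includes tolerance and adverse events, "Hospitalizations due to diseases related to progressive HIV-1-infection" and "Death due to diseases related to progressive HIV-1-infection". For days 0, 30, 180 and 360 the same section says that "blood samples will be collected to perform laboratory analysis (transaminases, CPK, serum lipid profile".

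**Known harms.** Interventions and safety of statins states that "The main risks of statins are elevation of hepatic enzymes, and myopathy". It gives 0.5% to 2.0% for transaminase elevation.

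**Analysis.** The Analysis plan sets intention-to-treat for efficacy and continues: "The outcomes viral load and CD4 T cells count, as well as most of tertiary/exploratory outcomes, are longitudinal data with repeated measurements". It then describes the GEE model. By-arm safety information appears only under Interim monitoring, where it goes to the DSMB. That section expects hepatic or muscle enzyme elevations in under 1%.

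**The concern.** The participants are asymptomatic and not yet due for antiretroviral therapy. Whether a year of lovastatin is worthwhile for them depends on harms as well as on viral load and CD4 count.

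A cause-restricted mortality outcome needs a judgement on cause for every death, and it drops any death judged unrelated to HIV. A death from liver injury or rhabdomyolysis would fall outside the outcome, although treatment may have caused it. The trial could then report on mortality in a sense narrower than its own hypothesis.

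The hospitalisation items raise a practical problem. If the monthly form follows Clinical follow-up, admissions for other causes may not be recorded as hospitalisations. The unrestricted outcome in Study outcomes could then not be filled as written.

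The enzyme and adverse-event data bear directly on the harms that the article names, yet none of them has the status of an outcome.

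**Working it through.** **1. Sections side by side**

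| Item | Background, hypothesis iv | Clinical follow-up | Study outcomes |
|---|---|---|---|
| Death | mortality, any cause | HIV-related only | HIV/AIDS-related only |
| Hospitalisation | within morbidity, any cause | progressive HIV disease only | no cause limit |
| Adverse events | not named | monthly | not listed |
| Transaminases, CPK | not named | days 0, 30, 180, 360 | not listed |
| Serum cholesterol | not named | lipid profile, same sampling days | listed |

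For death, the two methods sections agree with each other, and both are narrower than the hypothesis. For hospitalisation, they disagree with each other. For the harms data, collection is written and an outcome is not.

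**2. Where by-arm safety is stated**

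The interim reviews are set at six months and at the point when all patients complete nine months, while treatment lasts 12 months. For at least the last patients enrolled, events after month nine and the day-360 enzyme sample come after the final stated review. The article states no later by-arm summary of harms.

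**3. What 55 lovastatin patients can show**

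The article gives no expected rate of death or admission, so the size of that part cannot be computed. For enzyme elevation, the inputs are n = 55 per group (Sample size and power) and rates p of 0.5% and 2.0% (Interventions and safety of statins) and 1% (the upper limit of the expectation under Interim monitoring).

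Expected cases = 55p; chance of at least one = 1 − (1 − p)^55.

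| p | Expected cases | Chance of at least one |
|---|---|---|
| 0.5% | 55 × 0.005 = 0.28 | 1 − 0.995^55 = 24% |
| 1% | 55 × 0.01 = 0.55 | 1 − 0.99^55 = 42% |
| 2% | 55 × 0.02 = 1.1 | 1 − 0.98^55 = 67% |

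If none of 55 has an elevation, the one-sided 95% upper bound is 1 − 0.05^(1/55) = 5.3%.

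If the true rate on lovastatin were 5% against 1% on placebo, power at two-sided 0.05 would be about 23%; at 10% against 1%, about 54%. The 5% and 10% are assumptions, and the normal approximation is rough for events this rare.

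A final comparison of harms can therefore give counts and intervals by arm, but it is not a powered test.

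**The case against.** This is a journal article. By-arm tables of adverse events and laboratory shifts commonly sit in a full protocol or SAP, which is not shown. Study outcomes opens with efficacy, and keeping safety monitoring outside a ranked outcome list is a common layout. This stands: the absence of final safety tables is not a defect on its own.

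Three stronger readings are tempting, and the article does not support them.

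- *That no analysis of harms is planned.* Interim monitoring plans safety information by treatment group, names hepatic and muscle enzyme elevations, and leaves safety stopping to the DSMB. Clinical follow-up also uses the enzymes and serious adverse events for individual stopping.
- *That by-arm safety data stay with the DSMB for good.* The restriction belongs to the interim process and protects blinding while the trial runs. Randomization says that the allocation is disclosed after termination for data analysis, so nothing bars a final safety comparison.
- *That the clinical outcomes could never show harm.* As Study outcomes is worded, hospitalisations carry no cause limit and infections could rise on treatment. A non-HIV death or admission could also be recorded as an adverse event. It would not count in the mortality outcome or under the hospitalisation item of Clinical follow-up.

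These replies do not reach the definitions that the article fixes: the cause limit on mortality, its mismatch with the hypothesis, and the conflict over hospitalisations.

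**Conclusion.** The point holds in a limited form. The mortality outcome is restricted to HIV-related deaths, is narrower than the stated hypothesis and excludes death from toxicity or any other cause. Clinical follow-up and Study outcomes contradict each other on hospitalisations and must be reconciled. Adverse events, transaminases and CPK are in no listed outcome and no stated final analysis. This third part carries less weight, because a fuller document may supply it.

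The numerical consequence is modest. At the article's own rates, roughly 0.3 to 1.1 enzyme cases are expected on lovastatin. That assumes all 55 are followed and that the quoted rates apply to this population. The case for change rests on clear definitions and balanced reporting. The trial would not be expected to detect a difference in rare harms.

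**What to change.** 1. In Study outcomes, replace the HIV-related mortality item with all-cause death by arm, and define hospitalisation as all-cause by arm. Keep HIV-related cause as a subcategory of each, so that the comparison now intended is still available.
2. Reword the hospitalisation and death items in Clinical follow-up to match, so that the monthly record captures every admission and death with its cause.
3. List adverse events and elevations of transaminases and CPK as safety outcomes. Report them descriptively at the end of the trial: the number and proportion in each arm, and the between-arm difference, with exact 95% intervals.
4. If a full protocol or SAP already contains these items, align the outcome list with it.

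The enzyme and adverse-event data are already collected. The cost is a slightly wider recording item for deaths and admissions, revised wording and a few tables. No visit, sample, dose or stopping rule changes. The downside is imprecise estimates for rare events, which the report should state.
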